| BACKGROUND | Osteoarthritis (OA) is the most common rheumatological condition. Its distribution is universal. It is a public health issue because its socioeconomic consequences are considerable.  Physical treatments (spa treatment, muscle strengthening, etc.) are part of the recommendations for the therapeutic management of knee OA (EULAR, ACR, and the most recent recommendations, OARSI in 2010), but we lack a standardised protocol to optimise such treatments in clinical practice. In a recent publication, Forestier et al. showed, in a randomized multicentre study, "Thermarthrosis", the symptomatic efficacy of a standardized spa treatment protocol in knee OA on pain and function at 6 months. This standardized spa therapy includes 4 spa treatments: 1) hydrojets (individual), 2) massage/physiotherapy (individual), 3) mud applications (individual) and 4) balneotherapy (collective) repeated 6 days a week for 3 weeks. The results of this study show a beneficial effect of the treatment evaluated globally. This therapeutic action, whose philosophy is based on treatments carried out in discharge for a supporting joint, essentially involves their local sedative and anti-inflammatory action.  However, this type of care is sometimes considered tiring for patients who complain about its intensity and the difficulties of availability. Outpatient care, less intensive at a rate of 3 instead of 6 treatments per week but over a longer period of time combining standardised treatment and functional re-education, could be an interesting alternative to the current conventional treatment. After a sedative phase, it seems logical to recondition the patient for exercise by correcting the proprioceptive disorders and underlying muscle deficiencies, to prolong the long-term effectiveness of the spa treatment.  However, no study has evaluated the interest of combining a so-called sedative phase provided by spa therapy followed by an active approach of muscle strengthening and proprioception in knee OA. Moreover, no study has evaluated the factors predicting a good response to spa treatment. |
| MAIN OBJECTIVE | The main objective of the study is to compare the proportion of patients who achieved a composite outcome criteria combining the Minimal Clinically Important Improvement (MCII) in pain and/or functional ability and surgery of the target knee at 6 months with two types of spa therapy ("classical spa therapy" and "active spa therapy") in symptomatic knee OA. |
| Secondary objectives | The secondary objectives are to 1) compare the effectiveness of the two types of spa therapy on functional abilities and pain at the end of the treatment and at 3 months; 2) determine the evolution of quality of life scores (OAKHQOL, SF-36), fatigue, patient satisfaction, consumption of drugs and care, as well as the use of surgery in both types of spa therapy; 3) describe the effectiveness of the "classical spa therapy" in Nancy Thermal on pain and functional abilities by analyzing the before-and-after effect; 4) describe the postural anomalies encountered in patients with knee OA by posturographic analysis and evaluate the evolution of these anomalies according to the type of spa therapy over time; and 5) study the predictive response factors at 3 and 6 months |
| Main outcome criteria | The Minimal clinically important improvement (MCII) in OA was determined by F. Tubach et al. The MCII is a threshold for improvement that is particularly suitable for therapeutic trials and takes into account that the Minimal Clinically Important Difference (MCID) may be different for an improvement or a worsening. A patient is considered improved if the WOMAC index function subscale score is improved by at least 9.1 points from the initial value and/or if the current pain measured on a visual analog scale (VAS, 0-100 mm) is improved by at least 19.9 mm. These values correspond to the smallest clinically relevant change for these two outcome criteria. Improvements below this value will be considered as treatment failures. Patients with improvement but who would have still need to have surgery during the period of study will also be considered failures. The effect of two types of spa therapy ("a standard spa therapy" and an "active spa therapy") for symptomatic knee OA will be assessed by the proportion of patients who have achieved a composite criterion combining minimal clinically important improvement (MCII) for pain and/or functional abilities and the absence of knee surgery of the target knee at 6 months. |
| secondary outcome criteria | Secondary criteria   - Percentage of patients reaching MCII (pain, function and composite score) at the end of the treatment and at 3 months - Percentage of patients reaching the Patient Acceptable Symptom State (PASS) (pain and function) at 3 and 6 months. - Evolution of quality of life scores (OAKHQOL, SF-36) at 3 and 6 months - Evolution of VAS-fatigue, VAS-pain at 3 and 6 months - Evolution of WOMAC scores (function) at 3 and 6 months - Patient satisfaction (overall VAS or Health Education Impact Questionnaire **(**heiQ) module 9) at 3 and 6 months - Evolution of drug and care consumption, use of surgery - 6-minute walking test [43] - Evolution of posturography parameters: modification of the length travelled and/or the area covered by the pressure centre of the feet following the removal or disruption of sensory inputs, somesthesics of balance in distorted visual situations and static and dynamic positions [4] - adverse reactions |
| METHODOLOGY/ STUDY DESIGN | This is a single-centre, randomized, single-blind clinical trial of non-inferiority comparing "standard spa therapy" and "active spa therapy" in knee OA.  The patients in the standard spa therapy group will undergo a “classical spa therapy” according to the standardised care protocol defined in Thermarthrosis [1], that is, 1 daily session, 6 days a week for 3 weeks. The patients in the active spa therapy group will undergo therapy comprising thermal treatments of the classical spa therapy at a rate of 3 sessions per week for 3 weeks, followed by proprioceptive re-education and muscle strengthening at a rate of 3 sessions per week for 3 weeks. In both groups, patients will be allowed to take any additional medication and care that their referring physician deems necessary.  Randomization will be blinded and will use the Zelen method (randomization before consent is obtained).  Patients will be examined at 3 and 6 months by an evaluating physician, independent of the spa, who will be blinded to the patient's treatment group.  As a non-inferiority trial, the analysis will be per-protocol. |
| SUBJECT INCLUSION CRITERIA | Patients with knee OA:   - Meeting the criteria for knee OA of the American College of Rheumatology (*) - Uni- or bilateral OA - Symptomatic: VAS--pain > 3 on a scale of 0 to 10 - Radiological femoro-tibial knee OA³ stage 2 of the Kellgren and Lawrence classification - Providing consent - Preliminary medical examination   * The diagnostic criteria used are those of the ACR [Altman 1986]:   - Knee pain and at least 1 of the following 3 criteria:   - Age > 50 years old   - Morning stiffness < 30 min   - Crepitus on active motion - Presence of osteophytes on knee X-rays   (sensitivity 94%, specificity 87%) |
| CRITERIA FOR NON-INCLUSION | - Isolated patellofemoral OA - Indication for total joint replacement surgery within 1 year - Contraindication to spa therapy (immune deficiency, moderate to severe heart failure, cancer, infection, skin wound etc.) or predictable intolerance to spa therapy (intolerance to heat, baths, hot tubs, swimming pool etc.) - Other disease of the musculoskeletal system (inflammatory arthritis, disabling lumbar radiculopathy, motor deficit of the lower limbs) - Severe comorbidities - Severe depressive syndrome, psychosis - Previous knee treatments:   - Massages, physiotherapy, acupuncture of < 1 month   - non-steroidal anti-inflammatory drugs (NSAID) change within the last 5 days   - Change of analgesics within the last 24 hr   - Change of symptomatic slow-acting drugs in osteoarthritis of less than 3 months.   - Intra-articular injection of the target joint of < 1 month for corticoids and < 3 months for viscosupplementation   - Physiotherapy or rehabilitation of < 1 month.   - Spa therapy during the previous year |
| METHODS OF RECRUITING SUBJECTS | Information on the Nancy Thermal study will be provided to general practitioners and rheumatologists (mail and/or information meeting) in the months preceding the start of the study. Patient information will be provided through the press (regional press release and local radio stations) and by a poster campaign in the offices of physiotherapists, pharmacies, biological laboratories, and the waiting rooms of general practitioners and rheumatologists. A call centre will be set up to plan appointments with investigating physicians. |
| NUMBER OF SUBJECTS REQUIRED (PATIENTS, CONTROLS IF ANY) | Number of subjects required   - Main objective: with 50% responders to the standard spa therapy at 6 months [1], a power of 80%, and an alpha risk of 5%, 135 patients per group are required to significantly demonstrate the non-inferiority of the active spa therapy with a lower confidence limit of the difference in proportions of 15%. Considering that the number of patients lost to follow-up may be 5%, a total of 284 patients is needed in the trial. |
| LENGTH  DURATION | Expected inclusion period: January 2012 to the end of October 2012, i.e., 10 months  Duration of participation (including follow-up period): for a patient, 6 months from the beginning of the treatment  Total duration (including data analysis time): from December 2011 to mid-October 2013, i.e., 2 years |
| INVESTIGATION PROCEDURE DIFFERENCES FROM USUAL CARE | Spa therapy is performed according to the usual scheme for the "classical spa therapy”. The "active spa therapy” follows a pattern with fewer thermal care sessions, which are replaced by functional rehabilitation sessions by physiotherapists according to usual techniques.  The Nancy Thermal site does not yet have thermal approval and this study is carried out with this objective in mind. The chemical qualities of sodium chloride-containing water are identical to those of the Amnéville les Thermes spa.  Visits are made at inclusion, at the beginning of the cure, at 3 and 6 weeks and at 3 and 6 months. |
| EVALUATION OF RESEARCH BENEFITS AND RISKS | - The expected benefits are a reduction in pain, functional discomfort, and drug use and an improvement in quality of life.  - Adverse reactions that can be experienced with thermal treatment are rare, most often minor and transient. They are traditionally observed during the thermal treatment period and are then part of what is usually called the "thermal crisis": it is mainly a question of fatigue, awakening of certain pains during the thermal treatment phase, unusual sweating and insomnia. These effects rarely require the cessation of thermal treatments.  More serious health problems are possible with thermal treatment but remain exceptional: heart problems, infections linked to bacteria that may be present in warm waters (among them Legionella infection). |
| STATISTICAL ANALYSIS | **Descriptive statistics**  **Comparison of groups**  The trial being a non-inferiority trial, the main analysis will be a per-protocol analysis to be conservative by increasing the contrast between the groups.  Main objective  The active spa therapy will not be considered inferior to the standard spa therapy if the lower bound of the confidence interval at 90% of the difference between the 2 groups (active spa therapy minus standard spa therapy) for the main outcome criterion (percentage of respondents according to the composite criterion) is not less than 15%. After verification of the randomization that could be unbalanced due to the Zelen randomization mode, the final analysis will be adjusted if necessary on the variables that differ between the 2 groups.  Secondary objectives  - The same analyses will be repeated for the MCII composite criterion, pain and function at 3 months, and PASS criteria.  - To determine the predictive factors of spa therapy response, a bivariate analysis will be performed using chi-square tests (or Fisher exact tests depending on the number) for discrete variables and Student t-tests, ANOVA or Wilcoxon tests for quantitative variables. The parameters significant on bivariate analyses (at the conservative threshold of p=0.1) will then be introduced into a stepwise multiple logistic regression.  P<0.05 will be considered statistically significant.  The statistical analysis will be carried out by the Centre for Clinical Epidemiology by using SAS v9.2 (SAS Inc., Cary, NC). |
| EXPECTED FALLBACK | To be able to offer different types of spa therapy in order to adapt to patients' preferences.  Propose a spa therapy that can be performed externally near the patient’s home.  Offer a less tiring cure.  Obtaining thermal approval for the Nancy Thermal site. |

2. SCIENTIFIC RATIONALE AND GENERAL DESCRIPTION OF THE RESEARCH

Knee osteoarthritis (OA) is a common disease, the prevalence of which is increasing with age. Thus, an estimated 40% of the population over 75 years of age has OA [6]. In France, this represents 7.3% of the reasons for consultation in rheumatology, ahead of low back pain (6.1%) [7].

In addition to the important daily functional impact on patients, OA accounts for a considerable proportion of health expenditure, with direct costs estimated at €1.6 billion in France in 2002 [7]. These expenses are growing exponentially (+156% compared to 1993), due in particular to the ageing of the population and an increase in life expectanc, but also an increase in cost for patient care. Knee OA represents the third site in terms of frequency after lumbar OA and hand OA. Its painful and functional impact is important and the origin of pain is multifactorial: bone, inflammatory (effusion) and ligamentary [8].

Currently, knee OA is defined as a local disease characterized by destruction of joint cartilage and damage to other joint structures (bone, meniscus, synovium) and abarticular aspects (ligaments) even if some systemic factors may play a role. This disease may be aggravated by systemic factors (adipocytokines, growth factors, pro-inflammatory cytokines), vascular factors (arteriosclerosis of subchondral bone feeder vessels) and neurological factors (failure of the proprioceptive system) [9,10,11].

The diagnosis of OA is based on both clinical and radiographic features (joint space narrowing and bone reaction [osteosclerosis, osteophytes, geodes]) [5]. Biologically, we lack systemic inflammation and cartilage biomarkers for clinical follow-up or to judge the effectiveness of a treatment. Knee OA evolves for more than a decade, and the factors associated with clinical worsening and joint destruction are now better known and allow for better clinical evaluation of patients and thus a better optimization of research for therapeutic purposes [12]. Some risk factors are strongly associated with the aggravation of knee OA (malalignment, generalized OA) and others are moderately associated (intensity of symptoms at the beginning of the disease, duration of disease progression, synovial inflammation, ultrasonography and MRI findings, and hyper T2 signals of the trabecular bone on MRI) [8].

Therapeutic management of OA and in particular knee OA involves equal parts pharmacological and non-pharmacological treatment [13]. These treatments have effects on both pain and function and can be assessed by using algo-functional indices or quality of life scores. Therapeutic response criteria were determined and are commonly used (Minimal Clinically Important Improvement [MCII], Patient Acceptable Symptom State [PASS], OA Research Society International [OARSI] criteria) [2,14,15].

**Recommendations for the therapeutic management of knee OA**

A number of literature reviews and recommendations for practice are available for knee OA. These recommendations are regularly updated according to research progress: recommendations of the EUropean League Against Rheumatism (EULAR) [17], the American College of Rheumatology (ACR) [18] and OARSI in 2010 [13]. The Society of Medicine Physics and Rehabilitation (SOFMER) also made recommendations in association with the French Society of Arthroscopy (SFA)[16]. Although these recommendations depend on the methodological quality of the published studies, which are sometimes open to criticism, they nevertheless remain a reference and are widely distributed.

The analysis of the literature shows a modest effect of pharmacological treatments (paracetamol, NSAIDs, symptomatic slow-acting drugs in OA) [13]. Non-pharmacological treatments, including muscle strengthening, aerobic exercise and physical care seem to bring the same relief as pharmacological treatments but with a lower level of evidence owing to the complexity of the interventions and the methodology used (no long-term study, difficulties of double-blinding, etc.) [13]. Although the physical treatments (thermal cure, muscle strengthening etc.) are part of these recommendations, the interventions are not standardized, and the superiority of a specific technique or program compared to another has not been clearly established [13].

**Evaluation of crenotherapy**

Various good-quality thermal therapeutic trials have led to the recognition of spa therapy for treating chronic low back pain [19,20]. Several prospective randomized controlled trials have evaluated the effect of spa therapy for the main indications for crenotherapy in rheumatology: low back pain chronic, hip OA, hand OA, fibromyalgia, rheumatoid arthritis, psoriatic arthritis, spondylitis, chronic neck pain [21–35].

A number of these trials concern, at least in part, knee OA [36–42]. The estimated size effect of the treatment is 0.42, which corresponds to a moderate effect. [36, 39, 40]. In a recent article, Forestier showed in a randomized multicenter study, "Thermarthrosis", the efficacy of a standardized spa treatment protocol in knee OA on pain and function at 6 months [1]. This standardized cure involves 4 thermal treatments (hydrojets, massages, applications of mineral-matured mud at 45°C, balneotherapy) repeated 6 days a week for 3 weeks. The authors showed a symptomatic effect that remained evaluated globally and not according to its different components. This intervention, whose philosophy is based on care at discharge for a load-bearing joint also involves local sedative and anti-inflammatory care.

Although symptomatic efficacy may seem interesting, patients are more likely to sometimes complain about the intensity of this type of care, the fatigue and the difficulties with availability. External care, less intensive at a rate of 3 instead of 6 sessions per week but over a longer period of time, combining standardized spa therapy and rehabilitation, could be an interesting alternative to current conventional treatment. This approach combines the "sedative" action of spa therapy with muscular and proprioceptive strengthening. Indeed, after a sedative phase, it seems logical to recondition the patient for exercise by correcting the proprioceptive disorders and underlying muscle deficiencies, in order to prolong the long-term effectiveness of the spa treatment. However, no study has assessed the value of combining these two therapeutic approaches in knee OA.

**3. RESEARCH OBJECTIVES**

The purpose of this study is to compare the 6-month efficacy of two types of spa therapy: "standard spa therapy" (spa therapy delivered 6 days out of 7 for 3 consecutive weeks) and "active spa therapy” successively combining iterative spa sessions (3 sessions per week for 3 weeks) then specific re-education (3 sessions per week for 3 weeks).

The main objective of the study is to compare the proportion of patients with a composite response criterion combining the MCII for pain and/or functional ability and the absence of knee surgery on the targeted knee at 6 months, according to two types of spa therapy ("standard spa therapy" and "active spa therapy") in symptomatic knee OA.

The secondary objectives are as follows:

- To compare the effectiveness of the two types of spa therapy on pain and function at the end of the spa therapy and at 3 months

- To determine the evolution of quality of life scores (OAKHQOL, SF-36), of fatigue, patient satisfaction, medication use and care, as well as the use of surgery in both types of spa therapy

- To describe the effectiveness of standard spa therapy in Nancy Thermal on pain and functional abilities by an analysis of the before and after effect

- To describe the postural anomalies encountered with knee OA by a posturographic study and to evaluate the evolution of these anomalies according to the type of spa therapy and over time.

- To study the predictive factors of response to spa therapy (socio-demographic data, clinical, radiographic, ultrasonography and posturographic) at 3 and 6 months.

**4. STUDY DESIGN**

This is a single-centre, randomized, single-blind clinical trial of non-inferiority comparing "standard spa therapy" and "active spa therapy" in knee OA.

**3 weeks**

**6 weeks**

**M0**

**M3**

**M6**

**Inclusion**

**Randomization**

**standard spa therapy**

**Active spa therapy**

**End**

**d’étude**

Figure 1: Study design

**4.1. A PRECISE STATEMENT OF THE MAIN OUTCOME CRITERIA AND, WHERE APPLICABLE, SECONDARY OUTCOME CRITERIA**

Main Criterion

# The MCII in OA was determined by Tubach et al. [2]. The MCII is a threshold for improvement that is particularly suitable for therapeutic trials and takes into account that the MCID may be different for an improvement or a worsening. A patient is considered improved if the WOMAC index function subscale score is improved by at least 9.1 from the initial value and/or if the current pain measured on a VAS is improved by at least 19.9 mm. These values correspond to the smallest clinically relevant change for these two outcome criteria [2]. Improvements below this value will be considered treatment failures. Patients with improvement but would still need to have surgery during the study period will also be considered failures. The effect of the two types of spa therapy ("standard spa therapy" and "active spa therapy") for symptomatic knee OA will be assessed by proportion of patients who achieve a composite criterion combining the MCII for pain and/or functional abilities and the absence of knee surgery of the target knee at 6 months.

Secondary criteria

- Percentage of patients reaching the MCII (pain, function and composite score) at the end of the treatment and at 3 months
- Percentage of patients reaching the PASS (pain and function) at 3 and 6 months [14]. The PASS is the value beyond which the patient considers himself/herself to be well. It is defined as for the MCII by the 75th percentile of the score among patients whose assessment of the acceptable symptom state was “good” on a Likert scale with 5 answer modalities. The PASS for WOMAC function is 31 mm and for VAS for pain is 32 mm [14].
- Evolution of quality of life scores (Osteoarthritis Knee and hip Quality of life [OAKHQOL], SF-36) at 3 and 6 months
- Evolution of VAS-fatigue, VAS-pain at 3 and 6 months
- Evolution of WOMAC scores (function) at 3 and 6 months
- Patient satisfaction (overall VAS or heiQ module 9) at 3 and 6 months
- Evolution of drug and care consumption, use of surgery
- 6-minute walking test [43]
- Evolution of posturography parameters: modification of the length travelled and/or the area covered by the pressure centre of the feet after removal or disruption of sensory inputs, somesthesics of balance in distorted visual situations and static and dynamic positions [4]
- Adverse reactions

**4.2. DESCRIPTION OF THE RESEARCH METHODOLOGY, ACCOMPANIED BY ITS SCHEMATIC PRESENTATION SPECIFYING IN PARTICULAR THE VISITS AND EXAMINATIONS PREVUED.**

Collected data

Inclusion visit:

- Demographics: age, sex, level of education, current or former professional activity, place of residence (size of the municipality)
- Medical history and co-morbidities (Groll functional index)
- Medication
- History of knee OA: initial trauma (rupture of the cruciate ligament knee or lower limb fracture), presence of the symptoms before the current painful episode, duration of the current episode, previous drug treatments (corticosteroid injections, viscosupplementation, symptomatic treatments [analgesics, NSAIDs, symptomatic slow-acting drugs for osteoarthritis" (SySADOA)]) and non-drugs (surgery [osteotomy, arthroscopy, meniscectomy], spa treatment, rehabilitation, other etc.)
- Clinical data: weight, height, static disorders, length inequality of the lower limbs.
- X-rays of < 6 months with weight-bearing, full extended-knee X-ray and Schuss. The radiographs will be digitized for a centralized reading and will be used to confirm the diagnosis of femorotibial OA (Kellgren and Lawrence stage ≥2).
- Posturography examination
- Ultrasound examination

During other visits

Clinical and perceived health data will be collected before the cure (V0), at 3 weeks (V1: end of the standard spa therapy or change of type of care for active spa therapy), at 6 weeks (V2: end of active spa therapy), at 3 months (V3: M3) and 6 months (V4: M6) and will include the following examinations: clinical exam (effusion, joint amplitudes), VAS-pain, VAS-fatigue, WOMAC, OAKHQOL, SF-36, satisfaction, drug consumption, surgery, side effects, posturography examination, 6-minute walk. The number of treatments actually performed by the patients will also be collected.

The assessor will be blinded to the treatment group at 3 and 6 months.

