5.2. NON-INCLUSION CRITERIA

- Isolated patellofemoral OA
- Indication for total joint replacement surgery within 1 year
- Contraindication to spa therapy (immune deficiency, moderate to severe heart failure, cancer, infection, skin wound etc.) or predictable intolerance to spa therapy (intolerance to heat, baths, hot tubs, swimming pool etc.)
- Other disease of the musculoskeletal system (inflammatory arthritis, disabling lumbar radiculopathy, motor deficit of the lower limbs)
- Severe comorbidities
- Severe depressive syndrome, psychosis
- Previous knee treatments:
  - Massages, physiotherapy, acupuncture of M 1 month
  - NSAID change within the last 5 days
  - Change of analgesics within the last 24 hr
  - Change of symptomatic slow-acting drugs in OA of < 3 months
  - Intra-articular injection of the target joint of < 1 month for corticoids and < 3 months for viscosupplementation
  - Physiotherapy or rehabilitation of < 1 month.
  - Spa therapy during the previous year

**5.3. PROCEDURE FOR EARLY TERMINATION OF THE RESEARCH OR EXCLUSION (DISCONTINUATION OF TREATMENT + DISCONTINUATION OF FOLLOW-UP)**

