**Descriptive statistics**

Qualitative criteria will be described by their number and percentage and quantitative criteria by average, standard deviation or median and interquartile range (25th percentile- 75th percentile).

Results after treatment will be described by the number and percentage of responders according to the composite criterium, MCII pain, MCII function, PASS criteria and by the evolution of scores (means, standard deviation of differences) of self-questionnaires measuring health status.

To compare the evolution before and after treatment, matched t-tests will be carried out for quantitative assessment criteria and by testing McNemar for binary outcome criteria.

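### Within-arm before-after tests of care consumption lean toward an increase for the care types that the entry criteria bar, because use before selection is emptied and later use is free

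*Protocol*

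**What the plan says.** - **Criterion and objective.** Protocol section 4.1 lists "Evolution of drug and care consumption, use of surgery" among the secondary criteria, without a look-back period. Section 3 makes it an objective to determine the evolution of "medication use and care, as well as the use of surgery in both types of spa therapy".
- **Recording.** The follow-up table in section 4.2 marks care consumption at V0, V1, V2, V3 and V4, but not at selection.
- **Entry criteria.** Section 5.2 excludes patients with "Physiotherapy or rehabilitation of < 1 month" and with "Intra-articular injection of the target joint of < 1 month for corticoids and < 3 months for viscosupplementation". It also excludes spa therapy in the previous year. The summary gives 1 month for massage, physiotherapy and acupuncture. For NSAIDs, analgesics and slow-acting drugs, only a recent change is excluded.
- **After entry.** The summary (methodology) says that in both groups "patients will be allowed to take any additional medication and care that their referring physician deems necessary".
- **Analysis.** Section 9, under descriptive statistics, states: "To compare the evolution before and after treatment, matched t-tests will be carried out for quantitative assessment criteria". For yes/no measures, the same sentence names the McNemar test. Under comparison of groups, the secondary analyses between arms are limited to the MCII criteria at 3 months and the PASS criteria. The significance level is p<0.05.

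**The concern.** For the barred care types, the entry rule selects patients who have used none in the window before selection. If that window serves as the baseline, an individual's use can stay at zero or rise, but cannot fall. A paired test then compares a selected low point with ordinary follow-up, and a return to usual habits looks like a change after spa therapy.

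What is at stake is the reading of part of one secondary criterion within each arm. The distortion runs toward more care. It would not produce a false claim of reduced use, but it could hide a real reduction or report a significant increase that the therapy did not cause.

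**Working it through.** **1. Which stated analysis applies.** Section 9 contains three kinds of outcome analysis: paired before-after tests for assessment criteria in general; between-arm comparisons for the main criterion, the MCII criteria and the PASS criteria; and a regression for predictors of response. Consumption is not named in any of them. Only the paired rule is general enough to cover it, and it speaks of evolution, as the criterion does. That paired tests apply to consumption is therefore an inference, though the best-supported one.

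**2. Which items have a floor.**

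| Item | Entry rule | Floor before selection |
|---|---|---|
| Massage, physiotherapy, acupuncture, rehabilitation | none within 1 month | yes |
| Target-joint injection | none within 1 month (corticoids) or 3 months (viscosupplementation) | yes |
| Spa therapy | none within the previous year | yes |
| NSAIDs, analgesics, slow-acting drugs | no recent change | no: stable use continues and can fall |

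**3. How far the floor reaches V0.** Let w be the barred window before selection, g the gap from selection to V0, and L the look-back used at V0. The part of the look-back that falls in the barred window is min(L − g, w) if L > g, and zero otherwise.
- With g = 0 and L no longer than w, the whole baseline is emptied.
- With g at least L, none of it is.
- Inclusion opens in January 2012 (section 4.5, inclusion period) and the cures run from mid-March (section 4.5, group planning), so g can reach about 2.5 months for the first patients. At g = 2.5 months, a 1-month look-back does not overlap at all, and a 3-month look-back overlaps by 3 − 2.5 = 0.5 month.
- The protocol states neither L nor the usual g, so the size of the overlap is unknown.

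**4. Size in the limiting case (assumed zero baseline).** All discordant pairs then point one way, and with k later users the exact two-sided McNemar p is 2 × 0.5^k.
- k = 5: 2 × 0.03125 = 0.0625.
- k = 6: 2 × 0.015625 = 0.031.

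Six users are therefore enough for p<0.05. Take the 135 patients per group of section 9 and an assumed true later use r that treatment does not alter. The chance of a significant rise is P(X ≥ 6) with X binomial (135, r):

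| Assumed later use r | Expected users (135 × r) | Chance of p<0.05 |
|---|---|---|
| 2% | 2.7 | 5.5% |
| 3% | 4.05 | 22% |
| 5% | 6.75 | 67% |
| 10% | 13.5 | 99% |

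For contrast, with equal and independent use of 5% to 20% before and after, the simulated two-sided rejection rate in 135 patients is about 3%. The protocol gives no usage rates, so every r is an assumption. There is no protocol figure on this point to reproduce.

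**The case against.** The strongest reply is that the protocol nowhere says consumption will be tested before against after. The paired rule sits under descriptive statistics, next to responder and questionnaire results. The one explicit before-after objective is "To describe the effectiveness of standard spa therapy in Nancy Thermal on pain and functional abilities by an analysis of the before and after effect", which leaves consumption out. This stands as a limit on certainty. It does not remove the point, because no other stated analysis covers the criterion.

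Four stronger readings are tempting, and the documents do not support them.

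- **Care use must rise by construction.** Eligibility is checked at selection, consumption is first recorded at V0, possibly weeks later, and no look-back is stated. A zero baseline is not established, and with no later use there is no rise.
- **The whole drug and care criterion is distorted.** Apart from target-joint injections, drugs are barred only for a recent change. The expected benefit of lower drug use is not touched by this mechanism.
- **The arm comparison is biased.** Both arms share the entry criteria, so this mechanism favours neither.
- **Unequal visit spacing inflates later counts.** That would need consumption to be counted since the previous visit, which the protocol does not define. The derivation may be left to the SAP or the case report form.

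It is also true that section 4.2 collects previous treatments, including injections, spa treatment and rehabilitation, at inclusion. That history describes patients, but the plan does not make it the baseline for evolution, and its most recent part is emptied by the same criteria.

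**Conclusion.** The point holds in a limited form. For the barred care types, a within-arm paired comparison from V0 is biased toward an increase to the extent that the V0 look-back overlaps the barred window. The bias is complete if the look-back lies wholly inside that window and absent if V0 falls at least one look-back length after selection. In the limiting case, six later users in an arm are enough for p = 0.031. That figure rests on an assumed zero baseline, and the probabilities above also rest on assumed usage rates. The conclusion further assumes that the general paired rule of section 9 is meant to cover consumption. The drugs barred only for recent change, the randomised between-arm comparison and the primary endpoint are not affected.

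**What to change.** For massage, physiotherapy, acupuncture, rehabilitation, target-joint injection and spa therapy, state in section 9 that within-arm change from V0 will be neither tested nor interpreted as a treatment effect. Instead, compare the arms on use between V0 and month 6, either as the proportion of patients with any use or as a rate per patient-week. Leave out the spa and rehabilitation sessions that the study itself provides, since these would otherwise count as care.

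This changes only the wording of a secondary analysis. It needs no new data, since care consumption is already recorded from V0 to V4, and no change to entry criteria or permitted care. The downside is that these items lose a change-from-baseline figure.
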